**Figure 3 figure3:**
[figure not shown]
Image of the REST mobile app's profile screen. Pregnant women (participants) can monitor their pregnancy based on the results of the examination that have been input by the facilitator midwife and can also fill in the results of the examination carried out outside the implementation of the ANC class. ANC: antenatal care; REST: Risk Identification, Evaluation Counseling, Systematic Monitoring, Troubleshooting.

The fidelity of the intervention was assessed through a variety of strategies. First, the REST mobile app included an internal analytics system that automatically recorded user activities, such as examination results filled in by midwives and the completion of scheduled tasks by pregnant women (recording data on ANC visits). Second, the research assistant conducted periodic monitoring during ANC classes using a standard checklist to observe whether midwives and pregnant women were using the app according to protocol. Third, participants filled in the part of the delivery results they reported themselves. Any deviations from their intended use were documented and analyzed. This combined method allowed us to evaluate the compliance and quality of application usage across the cluster. The REST mobile app includes a built-in troubleshooting and decision support feature designed to assist midwives in early identification and management of maternal health issues. This feature operates on a rule-based algorithm that evaluates input data, such as blood pressure and hemoglobin levels against reference thresholds established by the Indonesian Ministry of Health and WHO guidelines. If an abnormal value is entered, the app automatically flags the entry and provides a visual alert. It then offers a set of recommended clinical actions, such as counseling, closer follow-up, or referral to a higher-level facility. Midwives retain clinical autonomy in making final decisions, but the app serves as a structured guide to enhance consistency and responsiveness in care. This feature was designed to strengthen early detection and ensure standardization in ANC service delivery, particularly in remote or resource-limited settings.

### Study Outcomes

All results were measured at the end of the study after participants from both the control and the treatment group had undergone labor. The success of the intervention was determined from the examination data input in the REST mobile app. Results were compared between the 2 groups. In addition, the effectiveness of the app was assessed using a questionnaire.

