**Methods:**

The research used the cluster randomized controlled trial (RCT) design, involving pregnant women from 11 subdistricts in Purworejo Regency, who were randomized to 11 clusters in the intervention group and 11 clusters in the control group. The 22 ANC class clusters comprised 22 midwives and 220 pregnant women. The intervention group received monitoring using the REST mobile app, while the control group received standard pregnancy monitoring in the antenatal care (ANC) class. The mentoring program included the use of the REST mobile app, which consists of pregnancy checks according to the 10T pregnancy examination standard. The app was used by midwives and pregnant women, starting from the second trimester of pregnancy to childbirth.

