## Introduction

The success of maternal health programs can be assessed through the main indicator of the maternal mortality rate (MMR). The gestation period is the focus of the main problem in preventing high MMRs, as it is during this time that the majority of risk factors for adverse maternal and fetal outcomes emerge. In particular, nutritional and metabolic issues, such as hypocalcemia, have been associated with complications in pregnancy, especially in resource-limited settings [1-3]. The gestation period is the focus of the main problem in preventing high MMRs. The World Health Organization (WHO) recommends that health workers improve consultation and care for pregnant women [4].

Antenatal care (ANC) services in normal pregnancy are provided at least 6 times: 2 times in the first trimester, 1 time in the second trimester, and 3 times in the third trimester. ANC examinations in normal pregnant women are carried out by a doctor at least 2 times in the first and third trimesters [5]. Failure in pregnancy care or ANC usually occurs due to social and economic factors, such as low education and family income, being too young or too old, living far from health facilities, unwanted pregnancy, and the consumption of illegal drugs [4].

The MMR in Central Java Province in 2021 was 199 per 100,000 live births (1011 cases), an increase compared to the MMR in 2020 of 98.6 per 100,000 live births (530 cases) and in 2019 of 76.93 per 100,000 live births (416 cases). Cases of maternal mortality increased from 2019 onward. The cause of disruption in maternal and child health services during the pandemic was due to major changes in health facility services and public health [6]. The still high mortality rate shows that the quality of maternal and neonatal services is not optimal. The issue of “3 late” is still the main problem in maternal health services, namely late decision-making, late arrival at the referral point, and late getting the services needed at health facilities. The low quality of pregnancy examination services is also reflected in the low compliance with ANC standards, which include 10 pregnancy examinations [7].

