## Methods

### Study Design

This research is an experimental study with a cluster randomized controlled trial (RCT) design. Cluster RCT is a research design that has multilevel characteristics. Generally, cluster RCT research uses 2 levels, the cluster or group level and the individual level. In this study, the class cluster will include pregnant women and participants of the ANC class. To minimize the risk of selection bias, we implemented the following strategies: (1) randomization at the cluster level was performed after cluster enrollment, and baseline characteristics of participants across the intervention and control groups will be carefully assessed and reported. The research design is described in Table 1.

**Table 1 table1:** Research design.

Group	Activity sequence 1			Activity sequence 2			Activity sequence 3			Activity sequence 4
	Observation	Intervention	Observation		Intervention	Observation		Intervention	Observation	
Control	O_0_^a^	X_0_^b^	O_1_^c^		X_0_	O_2_^d^		X_0_	O_3_^e^	
Intervention	O_0_	X_1_^f^	O_1_		X_2_^g^	O_2_		X_3_^h^	O_3_	

^a^O_0_: early identification in pregnant women in the first class of pregnant women.

^b^X_0_: standard intervention for routine antenatal classes without an app.

^c^O_1_: observations in the second class of pregnant women (trimester 2).

^d^O_2_: observations in the third class of pregnant women (trimester 3).

^e^O_3_: observation of childbirth and the newborn.

^f^X_1_: introduction of the REST (Risk Identification, Evaluation Counseling, Systematic Monitoring, Troubleshooting) mobile app for pregnancy monitoring for mothers and midwives using the 10Tpregnancy examination standard.

^g^X_2_: monitoring pregnant women after using the mobile app.

^h^X_3_: monitoring pregnant women using the mobile app and preparing for childbirth during the third trimester.

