Assessment of the results of the research will begin from the implementation of the first class of pregnant women. The total number of meetings was 3. The final result (a comparison of the expected outcome) was at the time of delivery. The research was carried out after ethical approval was obtained. The research locations are in 11 subdistricts in Purworejo Regency (Central Java, Indonesia): Loano, Purwodadi, Bruno, Butuh, Purworejo, Bagelen, Kaligesing, Kemiri, Kutoarjo, Ngombol, and Pituruh. These 11 subdistricts were chosen because they have health centers with inpatient services that make it easier for pregnant women to give birth in their areas.

Each ANC class group consisted of 10 pregnant women and 1 midwife. In each of the 3 meetings, an examination based on the 10T pregnancy examination standard was conducted, which included measuring the weight and height (T1), blood pressure (T2), mid-upper arm circumference (T3), uterine fundal height (T4), tetanus immunization (T5), iron supplement tablets (T6), fetal presentation and fetal heart rate (T7), counseling (including childbirth and postpartum preparation; T8), hemoglobin levels (T9), and care as needed (T10), as per the policy of the Indonesian Ministry of Health [5]. The results of the examination at each meeting were entered into the REST (Risk Identification, Evaluation Counseling, Systematic Monitoring, Troubleshooting) mobile app, and the pregnant women could see these results. If they performed a self-examination outside the ANC class schedule, they could fill in the results of the examination according to what they knew. Midwives and pregnant women were provided with training and a guidebook module for using the app. The control group carried out the standard ANC class without the use of the app, and they were exempt from recording examination results.

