##### Antenatal Care Visits

The REST mobile app records how many maternal examination visit are made to health facilities. Mothers with the REST mobile app who did not undergo examinations in accordance with the minimum ANC visit standard of ≥6 received a notification from their midwives to immediately carry out the examination.

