### Data Management

The data collected will be kept confidential for the duration of the study and disposed of after a period of 5 years. The data collection process from the beginning to the end of the study used 2 different methods. In the control group, data were collected using a form that was transcribed into electronic format, and in the intervention group, data were collected using an app and transcribed into electronic format that was stored on a desktop computer. These stored data will be used for further analysis. The individual appointed as the chair of the student project committee at the institute is responsible for overseeing data management.

To address missing or incomplete data, the researchers implemented proactive data validation and monitoring procedures within the REST mobile app. Real-time data entry validation rules were embedded in the app to minimize input errors and prevent incomplete submissions. In cases where data were missing or inconsistencies were detected, follow-up verification was conducted by the research team through direct contact with the respective participants or midwives, as appropriate. For statistical analysis, missing data will be assessed for patterns and mechanisms. Depending on the extent and nature of the missing data, appropriate methods, such as multiple imputation or complete-case analysis, will be used. To ensure overall data quality and accuracy, regular data audits will be performed, and all electronic data will be stored in secure, access-controlled databases with audit trails. These procedures have been designed to enhance data integrity and minimize bias due to incomplete or inaccurate information.

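### Table 2 stops assessing the ANC-visit primary outcome at month 3, which contradicts the text placing all outcomes at or after delivery and the whole-pregnancy standard of at least 6 visits

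*Protocol article*

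**What the plan says.** All references are to the protocol article.

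- **Timing in the text.** Study Outcomes: "All results were measured at the end of the study after participants from both the control and the treatment group had undergone labor". Study Design: "The final result (a comparison of the expected outcome) was at the time of delivery".
- **Timing in Table 2.** The ANC-visit row under Assessments carries an X at months 1, 2 and 3 and a dash after month 3; the footnote defines the dash as not applicable. In that last column, mode of delivery, birth weight and app use all carry an X. The close-out column is blank in every row.
- **Timing in Table 1.** After the observation at the third class, the only one left is at delivery, described as "observation of childbirth and the newborn".
- **The standard.** The Introduction sets the six visits as "2 times in the first trimester, 1 time in the second trimester, and 3 times in the third trimester". The study objectives and the Antenatal Care Visits section adopt at least 6 as the target.
- **Exposure.** The Abstract has the app in use "starting from the second trimester of pregnancy to childbirth". Under Antenatal Care Visits, app users below the "minimum ANC visit standard of ≥6 received a notification from their midwives to immediately carry out the examination".
- **Capture.** Data Management: "The data collection process from the beginning to the end of the study used 2 different methods", namely a form for controls and the app for the intervention arm. Study Outcomes adds: "The success of the intervention was determined from the examination data input in the REST mobile app".
- **Analysis.** Data Analysis fits a mixed effects linear model to the number of visits. Neither that section nor the outcome definition says when counting starts or stops.

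**The concern.** For a count outcome, the counting window is part of the definition. The article's timing statements and its assessment schedule give different windows for the same primary outcome, and no sentence reconciles them. A team that collects data by the schedule would stop before delivery, in the trimester where half of the standard visits are due and while the app is still in use and midwives may still be prompting women who are short of the target. If the app's effect on attendance arises late in pregnancy, a month-3 stop would miss part of it.

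The two arms also use different recording tools. When the end of the window is unclear and the tools differ, late visits may be recorded more fully in one arm than in the other.

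**Working it through.** **1. Is the dash in Table 2 genuine?** Each row has six entries, which match Week 1, Week 0, Months 1 to 3 and After month 3. The empty close-out column is common to all rows. The dash therefore does belong to the column after month 3. Because the delivery outcomes are marked in that column, it is the delivery period.

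**2. Where does month 3 fall?** The Population section gives entry at 20-22 weeks. Assumption: month 3 ends 12-14 weeks after entry.

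- Earliest: 20 + 12 = 32 weeks.
- Latest: 22 + 14 = 36 weeks.
- With months of 4 to 4.345 weeks, the latest value is 22 + 3 × 4.345 = 35.0 weeks.

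**3. How much of late pregnancy is left out?** Assumptions: third trimester from 28 weeks; delivery at D weeks; cut at c weeks. Share omitted = (D − c)/(D − 28).

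| Delivery | Cut 32 | Cut 34 | Cut 36 |
|---|---|---|---|
| 40 weeks | 8/12 = 67% | 6/12 = 50% | 4/12 = 33% |
| 37 weeks | 5/9 = 56% | 3/9 = 33% | 1/9 = 11% |
| 41 weeks | 9/13 = 69% | 7/13 = 54% | 5/13 = 38% |

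**4. What would that do to the count?** Take a woman who makes exactly the standard 2 + 1 + 3 visits and delivers at 40 weeks, with third-trimester visits spread evenly. The visits lost are 3 × 0.33 = 1.0 to 3 × 0.67 = 2.0.

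| Window | Count |
|---|---|
| First visit to delivery | 2 + 1 + 3 = 6 |
| First visit to month 3 | 6 − 2.0 to 6 − 1.0 = 4.0 to 5.0 |
| Enrolment to delivery | at most 1 + 3 = 4 |
| Months 1-3 only | at most 1 + 1.0 to 1 + 2.0 = 2.0 to 3.0 |

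The two first-trimester visits precede entry, so a target of 6 fits only a whole-pregnancy count. The figures in steps 3 and 4 are illustrative: the article gives no visit timing.

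**5. Is there a difference between arms?** The ANC-visit row has no arm footnote, so any cut applies to both arms. What differs is the recording tool. Study Design lets intervention women enter results obtained outside class and exempts controls from recording results. That makes unequal capture possible but does not show that it happened.

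**The case against.** The strongest reply is that Table 2 is a schedule of contacts and not a counting window. Its ANC-visit row has the same pattern as the routine ANC class row and the pregnancy complications row, so it may show only when data are taken at the three classes, with totals compared after delivery. Taken literally as a window, it would also exclude the first-trimester visits and make the target of 6 senseless. The Introduction's definition of six-visit coverage, the objectives and Study Outcomes all point to a whole pregnancy. This stands, and it is why the text is best read as intending a count to delivery. It does not remove the conflict: if data are taken only at the three classes, visits after the third class are still not collected, and the table calls that later assessment not applicable.

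It can also be said that month 3 is not tied to gestational age. Table 2's months run from allocation, and the intervention began after recruitment closed, so some women may have reached month 3 later than assumed. Table 1, which puts the second class in trimester 2, points the other way. This stands as a limit on the figures. Finally, the full protocol and the outcomes checklist are not shown, so the contradiction can be asserted only of the article.

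Two stronger readings are tempting. One is that the control arm alone was cut short, which would favour the app. The documents do not support it: the row applies to both arms, and Data Management describes collection from beginning to end in each. The other is that most women who reached 6 visits would be misclassified as falling short. That needs visit timings the article does not give, and it concerns a yes/no outcome, whereas Data Analysis models the number of visits.

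**Conclusion.** The contradiction is real and concerns a primary outcome: the schedule ends ANC-visit assessment at month 3, while the text and the standard behind the target require a count to delivery. If visits were in fact counted to delivery in both arms, the harm is confined to reporting. If the schedule was followed, roughly the last 4-8 weeks before a 40-week delivery are missing, or 33-67% of the third trimester. These are illustrative figures that assume month 3 falls 12-14 weeks after entry and the third trimester starts at 28 weeks. A cut common to both arms would lower counts and dilute a late effect; it would not create one. Unequal capture between app and form is a risk that the documents leave open, and no between-arm bias is shown. The point should be corrected, but it does not undermine the design.

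**What to change.** - Define the outcome in one sentence: all ANC visits from the first visit of the pregnancy to delivery, identically in both arms.
- In Table 2, mark ANC visits as assessed after month 3.
- Take the count in both arms from the same facility or midwife record, read after delivery, instead of from the app in one arm and the form in the other.
- If late visits prove not to have been captured in one arm, add a stated sensitivity analysis with a common month-3 cut in both arms.

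If both arms were already followed to delivery from a common record, the cost is one table cell and one sentence. Otherwise it is modest record abstraction for up to 220 women. Randomization and the planned mixed effects model are unchanged.

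### Outcome data come from the app in one arm and a form in the other, so recording differences cannot be separated from the app's effect, chiefly for ANC visits and complications

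*Protocol article*

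**What the plan says.** Four parts of the protocol article describe where outcome data come from.

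- **Study Outcomes** names a single source: "The success of the intervention was determined from the examination data input in the REST mobile app". The next sentence compares the two groups. Under Antenatal Care Visits, the capture of visits is described only through the app.
- **Study Design** has class examination results entered into the app and lets women add results from examinations outside class. For the other arm: "The control group carried out the standard ANC class without the use of the app, and they were exempt from recording examination results".
- **Data Management** states two methods: "In the control group, data were collected using a form that was transcribed into electronic format", while "in the intervention group, data were collected using an app and transcribed into electronic format". Real-time entry validation is described as built into the app.
- **Intervention** (paragraph after Figure 3) says the app logs user activity, including ANC visits. It adds: "If an abnormal value is entered, the app automatically flags the entry and provides a visual alert". In the same list of fidelity measures, "participants filled in the part of the delivery results they reported themselves".

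Randomization, Allocation, and Blinding says that neither provider nor participant could be blinded. Strengths and Limitations concedes performance and reporting bias on that account, but does not mention that the two arms were recorded differently.

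**The concern.** Three statements conflict: success is determined from app data, controls have no app and were exempt from recording, and controls have a data form. A reader cannot tell who recorded what for control women, when, or by what definition.

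Beyond the wording, the recording instrument is part of the intervention. An extra visit logged by an app user and an extra visit actually made look the same in the data. An unlogged visit lowers the count rather than appearing as a missing value, so imputation would not find it. The Intervention section nonetheless says that differences in outcomes can be attributed to the app. If recording differs between arms, that attribution fails for the outcomes most open to it.

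**Working it through.** **1. Can the analysis separate the two?** Data Analysis specifies mixed models with a cluster random intercept, a fixed effect for intervention and maternal covariates. Let A = 1 for app clusters and 0 for control clusters, b the true effect and r the effect of recording by app rather than form. Every app cluster uses one instrument and every control cluster the other, so on the model's scale the mean is

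a + b·A + r·A = a + (b + r)·A.

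Only b + r can be estimated. The random intercept and the covariates do not change this.

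**2. Which outcomes are exposed?**

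| Primary outcome | Described for the app arm only | Exposure |
|---|---|---|
| ANC visits | App logging; women's own out-of-class entries | High |
| Anemia, hypertension, chronic energy deficiency | Entry validation, alerts, out-of-class values | High, depending on how cases are classified |
| Mode of delivery, birth weight | Possibly self-report in the app | Lower: discrete events, with a delivery observation in both arms (Table 1) |

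**3. The plan's own figures, used as a scale.** Sample Size uses 0.92 and 0.72 with z values 1.96 and 0.842:

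(1.96 + 0.842)² × (0.92×0.08 + 0.72×0.28) / 0.20² = 54.02, stated as 54.

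Design effect: 1 + (10 − 1)×0.05 = 1.45. Then 54 × 1.45 = 78.3, rounded up to 79 per group. These reproduce. With 110 women per arm and no losses, the effective number is 110/1.45 = 75.9 per arm.

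**4. Illustration for six or more ANC visits.** Assumptions, none of them in the documents: no true effect, full capture by the app, and capture of a fraction s of qualifying women on the control form. The spurious difference is p × (1 − s). The chance of a significant result favoring the app uses the two-proportion normal approximation with 75.9 per arm; with no bias it would be 2.5%.

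| True rate p, both arms | s | Control appears as | Spurious difference | Chance of false benefit |
|---|---|---|---|---|
| 0.72 | 0.90 | 0.648 | 7.2 points | 16% |
| 0.72 | 0.80 | 0.576 | 14.4 points | 46% |
| 0.92 | 0.90 | 0.828 | 9.2 points | 40% |
| 0.92 | 0.80 | 0.736 | 18.4 points | 86% |

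**5. The direction can reverse.** If the form were complete and the app missed 10-20%, the same differences would count against the app. For complications, assume full detection in the app arm, 80% on forms and a true prevalence of 20-50%. The app arm would then show a spurious excess of 0.20×0.20 = 4 points to 0.50×0.20 = 10 points.

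**The case against.** Several stronger readings are tempting, and the documents do not support them.

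- **That controls have no outcome data.** The exemption in Study Design suggests this, but Data Management gives controls a form, Table 1 lists the same observations in both arms, and the assessment rows of Table 2 carry no restriction to one arm. The exemption may mean only that controls did not enter results in an app. This stands.
- **That the bias favors the app on visits.** Out-of-class entry was only advised, women entered what they knew, and Strengths and Limitations reports imperfect use and uneven internet access. App records could be the less complete ones. The notification to women below six visits prompts attendance, which is a real effect and not an artefact. This stands.
- **That alerts inflate complications.** The alert follows entry of a value and does not change it. If cases are classified from recorded values, the alert itself adds nothing. The article does not say how cases are classified, so this is a risk and not a demonstrated bias.
- **That all four primary outcomes are equally affected.** Mode of delivery and birth weight are discrete events, and the self-report sentence sits among fidelity measures and is not named as the outcome source.

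Data Management also describes follow-up of missing or inconsistent data by direct contact, and audits. These help with detected gaps, but they do not give the arms a common instrument. Finally, Sample Size does not say which outcome 0.92 and 0.72 describe, and the number of visits is to be analyzed by a linear mixed model. The binary illustration therefore shows scale and does not predict the trial's result.

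None of this removes the stated use of two methods or the conflict between the sections.

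**Conclusion.** The point holds in a limited form. The protocol states that outcome data were collected by app in one arm and by form in the other, and its sections disagree on the source of the outcomes and on what was recorded for controls. Instrument and arm coincide in an unblinded trial, and the planned models cannot undo this. The risk is greatest for ANC visits and for anemia, hypertension and chronic energy deficiency, and smaller for mode of delivery and birth weight.

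The direction and size cannot be derived from the documents. The range of about 7 to 18 points for six or more visits rests on assumed control capture of 80-90%, full app capture and equal true rates of 72% or 92%. A reader should not infer that a benefit on visits would be spurious, or that an excess of complications is to be expected.

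**What to change.** The abstract gives August 2024 to February 2025 for data collection, so a common form at the class meetings is no longer possible. What remains is retrospective harmonization.

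1. Reconcile Study Design, Study Outcomes and Data Management: for each primary outcome, state by arm the source, the recorder and the timing.
2. Replace the sentence that determines success from app data with a rule that each primary outcome uses the same source, definition and time window in both arms. The window matters because Table 2 schedules visit assessment for months 1 to 3 while app use continues beyond month 3.
3. Take ANC visits, mode of delivery and birth weight from midwife or facility records where available, abstracted in the same way for all 220 women.
4. Classify anemia, hypertension and chronic energy deficiency centrally from the raw values recorded at the scheduled class meetings, with identical thresholds in both arms and without out-of-class app entries.
5. Use app logs for fidelity only.
6. Report missingness by arm. Where no common source exists, add a sensitivity analysis over plausible capture rates in each arm, and name the differing instruments in Strengths and Limitations.

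The cost is modest abstraction work for 220 women. Some records may be missing, and the documents do not say whether facility records can be obtained. The sample size does not change.
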